### **Step 4: Assessment at one-month after treatment**

One month after the last face-to-face session, the researcher will post to each participant a same set of questionnaires as used for post-treatment assessment and a questionnaire for their feedback on their experience of the trial. The Participant Feedback Form includes both specific questions (intensity/workload, frequency and duration of the intervention) and non-specific questions (any questions raised by participants regarding the trial). The participant will be asked to complete and return the questionnaires within a week. If the questionnaires have not been returned within two weeks, the researcher will contact the participant by telephone to remind them and, if necessary, complete the questionnaires with the participant through the telephone.

### **Step 5: Interim analysis of individual data**

After receiving the completed questionnaires for one-month assessment, the researcher will analyse the results of individual participant for their baseline assessment, assessment immediately after treatment, and assessment at one-month after treatment. Both participants and the therapist will receive the individual result in mailing letters.

### **Step 6: Feedback session**

Within one week receiving the result of the interim analysis for individual participant, the therapist will contact the participant by telephone to deliver a feedback session. This telephone-delivered session will include the following content:

- 1) Discussing the results of the interim analysis. Informing participants of the results is part of the intervention. If participants have made improvement in clinical outcomes, this will encourage them to continue using the skills that they feel useful.
- 2) If there is no significant improvement after treatment or the participant could not maintain improvement in the past one month, potential problems and possible solutions will be discussed.
- 3) Discussing the skills that the participant continued to use during the past month and clarify reasons for not using certain planned skills.
- 4) Checking participants' understanding of this therapy and clarify any unclear aspects.
- 5) Discussing how to make further improvement and making a plan.

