## **Step 2: Six therapy sessions**

Participants will be invited to the Department of Psychology at the Astley Ainslie Hospital or the Clinical Research Facility at the Royal Infirmary of Edinburgh for therapy sessions. The intervention consists of six face-to-face sessions. A clinical psychologist, who is the therapist of this intervention, will provide support for the participant throughout the trial. During these sessions, the participant will discuss their fatigue-related problems with the therapist and work on a treatment manual to learn skills to overcome their fatigue. Each session will last about one hour and the first session will have an extra 30 minutes at the beginning to engage the participant in a collaborative therapeutic relationship with the therapist. There will be an interval of two weeks between sessions. During the intervals, the participant will be required to do some tasks at home, including keeping a diary, carrying out an activity plan, or reading sections of the treatment manual.

The intervention incorporates both psychological and rehabilitative approaches to challenge participants' cognition and behaviours in response to fatigue. With support from the therapist, the participant will explore their own problems in thoughts (their beliefs about fatigue and their ability to overcome it), emotions (their emotional responses to fatigue-related problems), and behaviours (physical activities in daily life) which may potentially contribute to their fatigue. Then they will work together to find out individualised treatment strategies to help the participant reduce the impact of fatigue on their daily life. The therapeutic components of the intervention, as well as the aim, rationale and expected outcomes for each component are summarised in Table 3.

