### **Step 7: Feedback meeting with participants**

After all individual feedback sessions completed, we will invite all of our 12 participants to a group meeting. This meeting will be at the Clinical Research Facility of Royal Infirmary of Edinburgh and a researcher will facilitate this meeting. During this meeting, we will invite our participants to share their experiences of taking part in this trial and to make suggestions for how their experiences of the trial, and of the therapy, could be improved. We will also explain that this intervention will be adapted to be delivered by nurses who visit stroke survivors in community, and will ask participants for their opinions on how this.

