#### 2) Therapy sessions

- Number of sessions each participant attended and reasons for reschedule or not attending
- Number of participants completing all sessions and reasons for withdrawal

An **Outline of Sessions** will be used to monitor attendance of each participant at treatment sessions. This form will be completed by the therapist for each

session to record the attendance, reasons for non-attendance, and withdrawal from the treatment.

Rate of participants completing the six treatment sessions will be calculated. If any participants withdraw from the treatment sessions, we will ask them for reasons (although they can withdraw at any time without giving any reason).

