## Data analysis

Descriptive statistics will be used to analyse the results. An interim analysis will be performed at one-month after the last face-to-face session. The final analysis will be performed at the end of the trial when all data collection, entry and validation are completed (three-month after the last face-to-face session). The data of feasibility will be analysed of a group of 12 participants. The clinical data will be analysed both individually and by group.

The number of participants attending, missing, and withdrawal (from therapy sessions and/or follow up) will be recorded and the relevant rates will be calculated. The success of

recruitment strategies will be measured by summarising responding, eligibility, and consent rated. The feasibility of assessment for clinical outcomes will be determined by the level of missing data of individual items and for the entire outcome questionnaires.

To investigate changes in clinical outcomes, we will report mean change in scores of each questionnaire with 95% confidence interval (CI) from pre-treatment assessment to post-treatment assessment. In addition, the change of scores for each clinical outcome from post-treatment to one-month follow up, and from post-treatment to three-month follow up, will be analysed to determine whether any benefits (if applicable) acquired during the therapy sessions could be maintained one month and three months after the last face-to-face session, respectively.

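### The three-month change cannot be read as maintenance of gains from the six face-to-face sessions, because a therapist-delivered telephone session falls between the one-month and three-month assessments

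*Protocol*

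**What the plan says.** Three sections of the protocol bear on this.

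- **Step 2: Six therapy sessions** gives the composition: "The intervention consists of six face-to-face sessions".
- **Step 6: Feedback session** comes after the one-month questionnaires have been returned and analysed for the individual. Then "the therapist will contact the participant by telephone to deliver a feedback session". On the results it says: "Informing participants of the results is part of the intervention". For a participant who has not improved, or has lost ground over the month, "potential problems and possible solutions will be discussed". The session also reviews which skills are still in use, checks understanding of the therapy, and ends with this item: "Discussing how to make further improvement and making a plan".
- **Data analysis** plans the change in each score from post-treatment to one month and from post-treatment to three months. The stated aim is to learn whether any benefits "acquired during the therapy sessions could be maintained one month and three months after the last face-to-face session, respectively".

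On delivery, the therapy-session part of the feasibility outcomes says: "Rate of participants completing the six treatment sessions will be calculated". Attendance at treatment sessions is logged by the therapist on the Outline of Sessions.

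**The concern.** To say that gains from a course of sessions were maintained, one needs an interval in which nothing further was delivered, or a comparison group that received the same further contact. This protocol has neither for the three-month point. Inside the interval it schedules a structured contact with the same therapist, and it calls at least the results part of that contact intervention.

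The content makes the direction of any distortion fairly clear. Problem solving is offered to the participants who failed to improve or to hold their gains. If the call helps, it raises the very scores that would have shown a loss of benefit, and so tilts the three-month comparison towards a finding of maintenance.

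The interpretation of the secondary before-and-after analysis is at stake, and so is clarity about the package under study. The protocol's stated aim is to define the intervention, yet its sections differ on whether the call belongs to it, and the reported completion rate covers the six sessions only.

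**Working it through.** No sample-size or power figure is involved. The check has three parts: the order of events, what the design can separate, and what is reported about delivery.

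**1. Order on the individual schedule**

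Inputs from the protocol:
- The one-month questionnaires are posted one month after the last face-to-face session, for return within a week. A telephone reminder follows if they are not back within two weeks (Step 4).
- The therapist calls within one week of receiving the individual result (Step 6).
- The three-month questionnaires are sent three months after the therapy sessions (Step 8).

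Assumptions, which the protocol does not fix: 1 to 3 weeks until return, 0 to 1 week for analysis and mailing, 0 to 1 week until the call, one month = 30 days, three months = 91 days.

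Time of call = 30/7 + return + analysis and mailing + call delay:
- earliest: 4.3 + 1 + 0 + 0 = 5.3 weeks after the last session
- latest: 4.3 + 3 + 1 + 1 = 9.3 weeks

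Three-month point: 91/7 = 13.0 weeks. The call comes first throughout this range, with 3.7 to 7.7 weeks to spare.

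**2. Order on the Timeline**

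The Timeline puts the feedback session in January 2015 and the three-month follow-up in March 2015. For a participant finishing on 30 November 2014, January is 4.6 to 8.9 weeks after the last session and March is 13.0 to 17.3 weeks. The order is the same.

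The two clocks do not agree for early finishers. Starting on 2 June 2014 with two-week intervals, six sessions span 10 weeks and end about 11 August. That participant's own three-month date is about 10 November 2014, whereas March 2015 is 28.9 to 33.1 weeks after the last session. The call would follow the three-month assessment only if calls were held back to January while follow-up ran on individual dates. That would apply to those finishing before about 2 October 2014 (1 January 2015 minus 91 days). Step 6 ties the call to each participant's own result, so its wording does not support that mixture.

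**3. What can be separated**

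For any score, write the mean change from post-treatment to three months as

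D3 = P3 + T,

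where P3 is the change that would have occurred after six sessions with no call, and T is the effect of the call, including being told one's results. The maintenance question concerns P3. The trial observes D3 only. It has no control arm (Trial design) and no assessment between the call and three months, so nothing identifies T.

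For one month, D1 = P1, because the call is triggered by the return of the one-month questionnaires. The difference D3 − D1 = (P3 − P1) + T mixes later drift with the call and does not isolate T either.

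**4. Delivery**

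Therapist contacts per participant rise from six to seven. The completion rate is defined on six. The Participant Feedback Form, which asks about intensity, frequency and duration, goes out with the one-month questionnaires and so precedes the call.

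**The case against.** The strongest reply is that the Data analysis section asks only whether benefits persist at a time counted from the last face-to-face session. It does not say they persist unaided, or because of six sessions alone. Step 8 describes the purpose as seeing whether gains are retained and whether more have been made, which suits a package with an openly declared telephone session. This stands in part: the three-month change is a true description of the participants' course and should still be reported. It does not rescue the wording in Data analysis, which ties the benefits to the therapy sessions and mentions no further contact.

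It is also fair to say that without a control arm the one-month change is not causally clean either. The claim here is narrower: one month is free of this particular contact.

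A reader might go further in three ways that the protocol does not support.

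- **That the group meeting in Step 7 is a second contaminating intervention.** It is led by a researcher, gathers experiences and suggestions, is listed as an acceptability measure, and is nowhere called treatment. Its trigger is "After all individual feedback sessions completed, we will invite all of our 12 participants to a group meeting", with a February 2015 slot. On individual three-month dates, anyone finishing before about 2 November 2014 would be assessed before it. It gives no ground for moving the meeting, which would delay information for the primary acceptability objectives.
- **That the call goes unmonitored.** The group meeting waits for all calls to be completed, and the therapist's own feedback meeting follows them, so completion has to be known. What is absent is a reported completion rate.
- **That the pilot trial will adopt a package on misattributed evidence.** Progression depends on acceptability and feasible processes, and effectiveness is left to the definitive trial.

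**Conclusion.** The point holds for the telephone session. Steps 2 and 6 differ on what the intervention comprises, and the maintenance reading in Data analysis is not supported at three months. On the individual schedule the call comes about 5 to 9 weeks after the last session and follow-up at about 13 weeks. This rests on the return and mailing times assumed above; the step order and the Timeline months give the same sequence. The effect of the call on any score is unknown and cannot be estimated from this design.

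The consequence is limited. The affected comparison belongs to the secondary objective, is descriptive, and rests on 12 participants. Recruitment, response rates, missing data and acceptability are not damaged, and the post-treatment to one-month change precedes the call. It would be wrong to infer that the three-month data are unusable; they describe the course after the whole package. The change is worth making because, as written, a report following the plan would credit the three-month result to the wrong set of contacts.

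**What to change.** 1. Reconcile Step 2, Step 6 and Data analysis so that they agree on whether the telephone session is part of the intervention. Which way to settle it is for the investigators.
2. In Data analysis, limit the maintenance reading for the face-to-face sessions to the post-treatment to one-month change. Describe the post-treatment to three-month change as the course after six sessions plus the telephone feedback session, and state that the two contributions cannot be separated.
3. Record delivery of the call, with its date, on the existing Outline of Sessions. Report its completion beside the six-session completion rate.

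The cost is a few sentences and one extra line on a form already in use. No visit, questionnaire, sample size or treatment content changes. While making the edit, it would help to state whether the call and the three-month follow-up run on each participant's own dates or on the Timeline's January and March 2015 slots, since these diverge for early finishers.

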### **Step 7: Feedback meeting with participants**

After all individual feedback sessions completed, we will invite all of our 12 participants to a group meeting. This meeting will be at the Clinical Research Facility of Royal Infirmary of Edinburgh and a researcher will facilitate this meeting. During this meeting, we will invite our participants to share their experiences of taking part in this trial and to make suggestions for how their experiences of the trial, and of the therapy, could be improved. We will also explain that this intervention will be adapted to be delivered by nurses who visit stroke survivors in community, and will ask participants for their opinions on how this.

### **Step 8: Three-month follow up**

Three months after the therapy sessions, the researcher will send each participant again the same set of questionnaires. This is to assess whether any gains the participant may have made could be retained and whether any further improvement has been made. The researcher will also write to each participant to inform them of the individual result of this assessment.

### **Feedback from the therapist**

After all the telephone-delivered feedback sessions, the Chief Investigator and the therapist will have a feedback meeting to discuss problems occurring during the intervention delivery and possible solutions. They will also discuss how to adapt this intervention to be delivered by stroke nurses.

### **Outcomes**

A combination of qualitative and quantitative measures will be used to address the research questions relating to the acceptability of the intervention and the feasibility of conducting a definitive trial in the future.

## Feasibility outcomes

### 1. Acceptability of intervention to therapist

- Consistency of therapist delivering the intervention

For each individual therapy session, we will provide a **Checklist of Session Content** to the therapist. This checklist contains important therapeutic components to be covered during each session. The therapist will also take notes for each session to record what has been discussed during the session and how cooperative the participant is during and between the sessions.

### 2. Acceptability of intervention to participants

- Feedback meeting after the feedback session
- Participant Feedback Form (completed by the participant one month after the last face-to-face session)

### 3. Feasibility of trial process

#### 1) Recruitment

- Number of discharge summary/clinical records/community survivors screened
- Number of survey questionnaires sent out
- Number of survey questionnaires completed and returned
- Number of people eligible for the trial
- Number of people consenting to participate the trial
- Reasons for non-participation and ineligible at each stage
- Comparison of recruitment approaches based on the stroke ward, stroke clinic and through the CHSS

#### 2) Therapy sessions

- Number of sessions each participant attended and reasons for reschedule or not attending
- Number of participants completing all sessions and reasons for withdrawal

An **Outline of Sessions** will be used to monitor attendance of each participant at treatment sessions. This form will be completed by the therapist for each

session to record the attendance, reasons for non-attendance, and withdrawal from the treatment.

Rate of participants completing the six treatment sessions will be calculated. If any participants withdraw from the treatment sessions, we will ask them for reasons (although they can withdraw at any time without giving any reason).

### 3) Three-month follow up

- Number of participants completing and returning questionnaires and reasons for not completing

### 4. Feasibility of assessment for clinical outcomes (for baseline assessment)

- Number of missing items of each questionnaire
- Reason for not or inadequate completing of certain items

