### *For trial design*

4. To test the feasibility of recruitment process
5. To determine the response rates of three-month follow up and missing data

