### *For clinical outcomes*

6. To test the feasibility of completing questionnaires for clinical outcomes

The secondary objective is to perform a before-and-after analysis of clinical outcomes.

- 1) Fatigue, measured by the Fatigue Assessment Scale (FAS) and by a Case Definition of post-stroke fatigue
- 2) Depression, measured by Patient Health Questionnaire-9 (PHQ-9)
- 3) Independence in daily life, measured by Nottingham Extended Activities of Daily Life (NADL)
- 4) Stroke-specific health-related quality of life, measured by Stroke Impact Scale (SIS)

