### **3) Final assessment and consent for participation**

At this meeting, each potential participant will meet the Chief Investigator of this study and a research nurse based at the CRF of RIE. The researcher will discuss with the potential participant any questions they may have about the study. The CRF nurse will help to check if this potential participant has adequate capacity in cognition and communication. This may identify a few people who are not eligible for the trial. For those patients, the researcher will explain why this trial is not suitable for them. Potential participants who are eligible for this trial and willing to take part will be asked to sign a consent form for taking part in the trial. This consent form will also be signed by the researcher and the CRF nurse.

After signing the consent, the participant will be asked to complete four of questionnaires for baseline assessment for the following clinical outcomes:

- Fatigue: Fatigue Assessment Scale (FAS) and a case definition for post-stroke fatigue
- Independence in daily life: Nottingham Extended Activities of Daily Living (NADL)
- Stroke-specific health-related quality of life: Stroke Impact Scale (SIS)

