#### **Clarification of the questionnaires**

If any item of questionnaires is unanswered or appears inconsistent with the other answers, or if the participants give inappropriate answers to the questions of the case definition, the researcher will clarify the reasons with the participant.

Finally, the participant will be asked to choose a date from a list of dates for the first therapy session (the list is provided by the therapist before this meeting).

For each participant, the researcher will send a letter to inform their GPs that they are taking part in this trial for post-stroke fatigue.

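### The only listed count of missing items is confined to baseline, although objectives 5 and 6 and the data analysis section carry no such limit, so item gaps on the follow-up forms may go unmeasured

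*Protocol*

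**What the plan says.** - **Outcome list.** Feasibility outcomes, item 4, carries the heading "Feasibility of assessment for clinical outcomes (for baseline assessment". Its first measure is "Number of missing items of each questionnaire"; its second is the reason why items were left out or poorly completed. No other listed outcome counts items.
- **Three-month outcome.** Feasibility outcomes, item 3, part 3, records how many participants complete and return the questionnaires, with reasons where they do not. It works at the level of the participant and the form.
- **Objectives.** Objective 5 is "To determine the response rates of three-month follow up and missing data". Objective 6 is "To test the feasibility of completing questionnaires for clinical outcomes". Neither is confined to baseline.
- **Data analysis.** Feasibility of assessment is to be "determined by the level of missing data of individual items and for the entire outcome questionnaires". No time point is named.
- **Baseline setting.** Under Final assessment and consent for participation, the FAS, the case definition, the NADL and the SIS are completed at the meeting in the research facility. Under Clarification of the questionnaires, "If any item of questionnaires is unanswered or appears inconsistent with the other answers", then "the researcher will clarify the reasons with the participant". The PHQ-9 is not in this pack. It is collected in the Stage 1 survey, returned by post, and used for screening in Table 2.
- **Follow-up setting.** The five post-treatment forms are taken home (Step 3), the one-month set is posted (Step 4) and the three-month set is sent (Step 8). Steps 3 and 4 allow telephone completion when forms do not come back; Step 8 does not mention it.

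**The concern.** The outcome list is narrower than the objectives it serves and narrower than the analysis text. A team working from the outcome list would tally missing items once, before treatment. A team working from the Data analysis section would tally them at every assessment. The two would report different answers to the same primary objectives.

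The single time point chosen is also the one with most support. Four of the five baseline instruments are filled in with a researcher present who raises blank items, and the protocol describes that step only for the baseline meeting. Every change score planned in Data analysis needs at least one follow-up form, and two of the three contrasts (post-treatment to one month, post-treatment to three months) use follow-up forms alone. Item gaps there bear directly on the before-and-after analysis and on what this study can tell the planned pilot about its outcome measures, one of the aims in Table 1. As listed, no outcome would show them.

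**Working it through.** **1. The plan's own figure.** Stage 1 assumes 100 people approached, 50% responding, 30% of those eligible and 80% of those agreeing: 100 x 0.50 x 0.30 x 0.80 = 12. This reproduces the stated sample of 12, which is used below.

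**2. Inputs for coverage.** There are 12 participants (Participants) and four assessments: before treatment, immediately after, one month and three months (Clinical outcomes). Four instruments are completed at the baseline visit (FAS, case definition, NADL, SIS). One pre-treatment PHQ-9 per participant appears to come from the survey. Five instruments are used at each of the three follow-ups (Steps 3, 4 and 8). Full retention is assumed.

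**3. Forms.**
- Baseline, at the visit: 12 x 4 = 48.
- Baseline, survey PHQ-9: 12 x 1 = 12.
- Baseline total: 48 + 12 = 60.
- Follow-up: 12 x 5 x 3 = 180.
- All: 60 + 180 = 240.
- Covered by item 4 as headed: at most 60/240 = 25%. Follow-up forms covered: 0 of 180.

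By assessment occasion the share is the same: 12 of 12 x 4 = 48, or 25%.

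**4. The passages side by side.**

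| Place | Item-level count? | Time point |
|---|---|---|
| Objective 5 | Missing data, level not stated | Named together with three-month follow-up |
| Objective 6 | Completion of questionnaires | None given |
| Feasibility outcomes, item 3, part 3 | No; completed and returned forms | Three months |
| Feasibility outcomes, item 4 | Yes | Baseline |
| Data analysis | Yes, plus whole questionnaires | None given |

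The only row that both counts items and fixes a time point fixes it at baseline.

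**5. Size of any bias.** The protocol gives no missing-item rate for either mode, so none can be computed. For scale only, if the chance that a form has a missing item were assumed to lie anywhere from 2% to 30%, the expected number of incomplete forms among 12 would run from 12 x 0.02 = 0.24 to 12 x 0.30 = 3.6. Nothing in the document places the supervised visit or home completion within that range, and a baseline count cannot locate the home figure.

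**The case against.** The strongest reply is that the baseline limit stands in one parenthesis. Data analysis has no such limit, and it also says that numbers missing or withdrawn from follow-up will be recorded and rates calculated. Whole-form return at three months is a listed outcome. A reader might infer that the plan as a whole measures missing data only at baseline; the documents do not support that. What remains is an inconsistency at item level, with the restriction explicit in the list that defines the outcomes.

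Four further inferences go too far:

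- **That the PHQ-9 cannot be evaluated.** A pre-treatment PHQ-9 exists from the survey, the Clinical outcomes section lists depression among the pre-treatment measures, and the form is in every follow-up pack. What is unclear is whether item 4 counts the survey form.
- **That the covered share is 48 of 228, or 21%.** That leaves out the 12 survey PHQ-9 forms.
- **That completion will be found feasible by construction.** The clarification step asks for reasons. It does not say that blank items are then filled in, or that the count is taken after the query, and it fits naturally with item 4's own measure of reasons. Optimism is the likely direction but is not shown.
- **That baseline uses a different mode from the later trials.** The protocol does not say how questionnaires will be administered in the pilot or the definitive trial.

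It is also fair to say that studying reasons for blank items at the one face-to-face assessment is defensible, and that reporting by mode is detail an analysis plan may hold. Neither removes the mismatch between the outcome heading and the objectives.

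**Conclusion.** The point holds as an inconsistency within the protocol that has a practical consequence. Followed as written, the outcome list leaves item-level missingness unmeasured on all 180 follow-up forms and covers at most 60 of 240 (25%). These counts assume 12 participants, full retention, and that the survey PHQ-9 serves as the baseline PHQ-9. A share of forms describes coverage; it is not a measure of bias.

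Baseline is a weak guide to home completion because 48 of its 60 forms are completed in person with blank items queried. That it is also an optimistic guide is a judgement about the likely direction, and its size is unknown. The change is worth making because it bears on two primary objectives and the data will already be in hand.

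**What to change.** Delete the parenthesis in the heading of Feasibility outcomes, item 4, so that it agrees with objectives 5 and 6 and with Data analysis. In the same item:

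1. Count missing items per questionnaire at all four assessments.
2. Take the count from the form as first completed or returned, before any researcher query.
3. State that the survey PHQ-9 is the baseline PHQ-9 and is included in the count.
4. Report the counts by mode of completion: in person, home or post, telephone.

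The cost is a small extra tally and a note of mode on forms that are already collected. Participants are asked for nothing more.
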